### Study design and period

A multi-center prospective open cohort study design on COVID-19 confirmed cases in Ethiopia conducted from December 01, 2020 to December 2021. Like many other disease-specific general open cohorts, such as in Framingham Heart Study and the Ethiopia Netherlands AIDS Research Project (ENARP) studies, the study intends primarily to measure the incidence of several epidemiological, clinical, virological, and immunological outcomes of COVID-19 cases [29, 30]. The cohort will be an unbiased extensive routine collection of clinical, radiographic, laboratory, and clinical management, virological, immunological and nutritional data, which helps to detect and address emerging research priorities without relying on a priori hypothesis.

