### Primary outcome and secondary outcomes

The primary outcome variables are treatment outcome (active cases, recovered, death or transferred for further treatment), recovery time, and duration of viral shedding (the time from the first positive RT-PCR results to the occurrence of the last positive RT-PCR results or negative RT-PCR results). The secondary outcomes include clinical symptoms and signs (major); co-morbidities; status at last follow-up (survival, severity, virus detection); laboratory biomarkers; duration of symptomatic phase, inpatient stay, ICU stay; viral loads; anti-SARS-CoV-2 antibody titer; imaging with results; therapeutic measures; plasma 25-hydroxyvitamin D concentrations; dietary history; micronutrient status (zinc and vitamin A); fasting blood sugar; weight, height, BMI; total cholesterol (TC), triglycerides (TG), HDL-C, LDL-C and body composition(waist circumference); genetic frequency shifts (genotypic variations); obstetric and gynecologic history; pregnancy status/test; clinical status; supplemental oxygen; non-invasive ventilation or oxygen delivery devices/ respiratory support. We will also collect confounding variables include socio-demographic variables (age, sex, education status); status cases at the time of enrollment; and months after the first positive test.

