To take into account the multi-center cohort design, i.e., clustering of data by treatment centers and repeated measurements per subject over time, a multilevel modeling approach will be employed using mixed-effects modeling or generalized estimating equation. Incomplete data (missing values and lost-to-follow-up cases) will be handled using model-based approaches, such as full information maximum likelihood estimation and multiple imputation modeling after the missing data mechanisms and assumptions are evaluated. Regression models will be evaluated for potential problems including collinearity among predictors, omitted variables bias, and model over-adjustment (endogeneity). The final fitted models will be assessed for validity and robustness of results on a subsample of data not used in the model-building procedure. For this purpose, a random subsample from the original data will be kept before starting the analysis. Statistical significance will be considered at α < 0.05. However, to control for the inflated probability of Type-I error due to multiple hypotheses testing, P-values will be adjusted for false discovery rate using the Benjamini–Hochberg method. The results will be described as percentages, tables, figures, and association significance.

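### Calendar time is neither a listed confounder nor a model term in a year-long open cohort, so a factor with no effect can look prognostic if its frequency and the outcome risk both drift

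*Protocol article*

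**What the plan says.** Under Study design and period, the protocol article describes "A multi-center prospective open cohort study design on COVID-19 confirmed cases in Ethiopia", "conducted from December 01, 2020 to December 2021". It gives no separate enrolment window. The section on sample size and sampling procedures adds 12 months of follow-up after enrolment.

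Under Primary outcome and secondary outcomes, it states: "The primary outcome variables are treatment outcome (active cases, recovered, death or transferred for further treatment), recovery time, and duration of viral shedding". Shifts in virus genotype frequency are a secondary outcome. The confounders to be collected are age, sex and education, then "status cases at the time of enrollment; and months after the first positive test".

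Under Data processing and statistical analysis, factors that pass a bivariate screen go into a multivariable model, with Cox models for time-to-event outcomes. The multilevel approach is there to handle "clustering of data by treatment centers and repeated measurements per subject over time". The same section promises a check for omitted-variable bias without naming a variable, validation on a random subsample set aside beforehand, and Benjamini–Hochberg adjustment.

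**The concern.** The research question is whether host factors and environment influence outcomes, and the aims add diet and treatment. In an open cohort patients can enter at different points of the epidemic. Over a year the virus mix, the care in force, hospital load and case mix may all change, and some of the factors under study may change with them. Months since the first positive test does not capture this: two patients admitted eleven months apart can have the same value.

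If calendar period is not in the model, part of any period difference in risk is credited to whichever factors became more or less common over the same months. The planned safeguards do not deal with it:

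- A random hold-out comes from the same months and shows the same confounded association.
- Centre effects remove differences between centres, not trends within a centre.
- False-discovery control addresses multiplicity, not bias.
- The bivariate screen tests candidate predictors, and calendar time is not named as one.
- Genotype could stand in for period only in part, and the article does not say that every patient's virus is sequenced.

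**Working it through.** The article has no figure on this point to reproduce. The check asks how large an association a null factor could show.

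**Inputs from the article (sample size section):** 6,390 patients, 28% death rate, design effect 2.5, 20% loss to follow-up. Patients with follow-up: 6,390 × 0.8 = 5,112. Effective number after the design effect: 5,112 / 2.5 ≈ 2,045.

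**Assumptions:** two equal calendar halves; a factor with no effect within either half; death risks r1, r2; factor prevalences e1, e2. None of the drift sizes is in the article.

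**Formulas:**
- Risk with the factor: pE = (e1·r1 + e2·r2) / (e1 + e2)
- Risk without it: pU = [(1−e1)·r1 + (1−e2)·r2] / (2 − e1 − e2)
- Crude OR = [pE/(1−pE)] / [pU/(1−pU)]
- z = (pE − pU) / √[p(1−p)(1/nE + 1/nU)], where p is the overall risk; after the design effect, z/√2.5 = z/1.58

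**Worked example** (risk 22% then 34%, prevalence 30% then 70%): pE = 0.3×0.22 + 0.7×0.34 = 0.304; pU = 0.7×0.22 + 0.3×0.34 = 0.256; OR = (0.304/0.696)/(0.256/0.744) = 1.27. With 2,556 patients in each group, z = 0.048/√(0.28×0.72×2/2,556) = 3.82, or 2.42 after the design effect.

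**Overall risk held at 28%:**

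| Risk, half 1 → 2 | Prevalence, half 1 → 2 | Crude OR | z, n = 5,112 | z after design effect |
|---|---|---|---|---|
| 28% → 28% | any | 1.00 | 0 | 0 |
| 25% → 31% | 40% → 60% | 1.06 | 0.96 | 0.60 |
| 22% → 34% | 40% → 60% | 1.13 | 1.91 | 1.21 |
| 22% → 34% | 30% → 70% | 1.27 | 3.82 | 2.42 |
| 18% → 38% | 20% → 80% | 1.83 | 9.55 | 6.04 |

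**Lower starting risk of 10%:**

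| Change in odds (risk) | Prevalence, half 1 → 2 | Crude OR | z, n = 5,112 | z after design effect |
|---|---|---|---|---|
| ×2 (10% → 18.2%) | 20% → 60% | 1.32 | 3.43 | 2.17 |
| ×2 (10% → 18.2%) | 30% → 50% | 1.15 | 1.72 | 1.09 |
| ×1.5 (10% → 14.3%) | 20% → 60% | 1.18 | 1.91 | 1.21 |

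Adjusting for calendar half returns the odds ratio to 1.00 in every row, by construction. If only risk or only prevalence drifts, there is no bias. These are crude two-by-two figures for a binary outcome. The mechanism is the same for recovery time and shedding, but no size was computed for those.

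**The case against.** The strongest objection is that this is detail for a fuller document. The article condenses a protocol, and the analysis plan is not shown. The confounder sentence says what will be collected and is worded as a list of inclusions, not a closed adjustment set. Nothing forbids admission month as a candidate predictor, and a check for omitted-variable bias is promised. This stands to the extent that calendar time may be handled elsewhere. It does not dispose of the point, because the article names its confounders, chooses a time axis that runs within the patient, and states a selection rule under which a confounder can drop out.

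Second, some drift would be absorbed. Age and status at enrolment are listed confounders, and treatments, comorbidities and respiratory support are recorded. A change in admission threshold would act largely through status at enrolment. This also stands: a multivariable estimate should be less biased than the crude figures, though not free of period effects.

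A reader might go further in three ways that the article does not support:

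- **That any factor whose frequency changes will be biased.** Outcome risk must drift as well.
- **That the large sample makes such bias statistically significant.** Several scenarios fall below 1.96 even at n = 5,112. The odds ratio of 1.32 falls from z = 3.43 to 2.17 once the design effect is allowed for, before any multiplicity adjustment.
- **That the authors expect the genotype mix to shift.** They plan to measure shifts and forecast nothing.

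Finally, the spread of entry dates is inferred. Twelve months of follow-up after enrolment fits a December 2021 end only if nearly everyone entered in December 2020. With entry that compressed the concern would shrink, but an open design implies staggered entry.

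**Conclusion.** The point holds in a limited form. As written, the plan adjusts for time since a patient's own positive test, for centre and for repeated measures, and leaves calendar period uncontrolled. The resulting bias is possible, not demonstrated. It needs both outcome risk and factor frequency to drift, and the article gives no size for either. Under the assumed drifts the crude odds ratio for a null factor runs from about 1.06 to 1.3, and higher if drift is extreme. It is not always significant, and part of it would go with adjustment for age and status at enrolment. The conclusion rests on entry being spread over the year, which the open design implies but the follow-up schedule puts in doubt. The change is worth making because it is cheap and none of the planned safeguards replaces it.

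**What to change.** 1. Under Primary outcome and secondary outcomes, add the calendar date of admission, or of the first positive RT-PCR, to the confounders.
2. Under Data processing and statistical analysis, state that this date enters the multivariable models for the primary outcomes, as calendar quarter or a spline, regardless of the bivariate screen. Adjust the Cox models for calendar period or stratify them by it.
3. State the enrolment window, and reconcile 12 months of follow-up after enrolment with the December 2021 end.

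Reporting factor associations by period is optional.

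The cost is wording and a few degrees of freedom per model, against a planned 6,390 patients. The article does not say outright that the dates are recorded. They should be available, since screening is timed from admission and shedding from the first positive RT-PCR.

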### Data collection

Data collection will be done electronically using the REDCap software package and data documentation will be performed from a retrospective history of the patient and prospectively after treatment is finalized. Contact information such as home address and telephone number will be collected to facilitate follow up and for tracking defaulters of follow-up. For asymptomatic cases whose follow-up is undertaken at home, their home address, GPS coordinates and geospatial data for all participants will also be registered by trained data collectors (study nurse or doctor). Data will be gathered from patients and follow up cases through interviews by physicians/nurses at each treatment center using a questionnaire and standardized Case report form (CRF). Biological samples will also be collected at baseline and follow up when samples are taken in the context of care to meet the research objectives. Five-milliliter venous blood will be collected using a serum separator tube and 4 mL venous blood will be collected using a test tube containing anticoagulant. Viral load measures in a body fluid using Abbot and Rosh reagents and platforms will be measured. Phylogenetic analysis of SARS-CoV-2: genotyping of different types of SARS-CoV-2 from Ethiopian isolates under different settings will be done using a next-generation sequencer at Ethiopian Public Health Institute (EPHI). Imaging: chest x-ray, ultrasound scan, chest computed tomographic (CT) scans data will be retrieved if available. Laboratory tests for D-dimers, platelet count, PT, PTT, INR, D- Dimer, and serum ferritin will be measured.

The screening will be performed within the period between one to two days of admission to the hospital to review study inclusion/exclusion criteria; obtain prior medical and concomitant medication histories; perform a complete physical examination, including height, body weight, and vital signs (blood pressure, BP, heart rate, HR), Oxygen saturation (SpO2) with pulse oximetry; and collect a blood sample for laboratory testing on screening day.

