### Study population

This study will enroll individuals with confirmed infection with COVID-19 at selected Federal and Regional Hospitals irrespective of their differences (age, sex, symptoms, severity, and any other conditions). The patients' follow-up will be done strictly within the management adapted to their infection.

Individuals/patients in the study hospital or area will be eligible for inclusion if they meet the following criteria: (1) patient is admitted to selected treatment centers (Federal and Regional’s Hospitals) with COVID-19 confirmed by RT-PCR; and (2) consents to be enrolled in the follow-up study and provide all necessary information/data, blood sample, and nasopharyngeal swab for testing. Patients will be excluded if: (1) a subject deprived of freedom, subject under a legal protective measure; (2) refusal by a participant, parent or appropriate guardian or representative; (3) not willing to stay 12 months in the cohort in Ethiopia; (4) is already involved in the COVID-19 clinical trial or other interventional studies; (5) not capable of understanding or complying with the study protocol or provide consent; (6) anticipated transfer to another hospital that is not a study site within 72 h.

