### Sample size and sampling procedures

The estimated sample size for this study is 6,390, based on the assumptions of a 28 percent death rate from a retrospective study, a design effect of 2.5, and a 20 percent loss to follow-up. A baseline evaluation or assessment will be performed immediately after screening. After baseline assessment, all patients will be followed-up daily until discharge according to WHO and National discharging guideline and followed as per schedule after discharged. Study subjects enrolled will be followed up for 12 months after enrollment for the specific objective related to virology and immunology, clinical course of the disease, response to treatment, effect of COVID-19 in pregnant mothers and birth-related effects of COVID-19. Enrolled cases will be followed up at 2 weeks, 3 months, 6 months, 9 months, and 12 months post-discharge. A visit window of ± 7 days may be applied to these visits. Patients discharged after recovery will be followed up according to the follow-up schedule.

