### Follow-up visits

Data collection at follow-up at 2 weeks, 3 months, 6 months, 9 months and 12 months was the same as at baseline and used to ascertain primary and secondary outcomes. The following tasks will be performed at these visits:Perform symptom-Directed physical exam,Obtain body weight and vital signs including pulse, respiratory rate and blood pleasure, oxygen saturation,Perform pulmonary function test (PFT),Record any symptoms,Spirometry to determine pulmonary function tests such as forced expiratory volume in the first second (FEV1), forced vital capacity (FVC) and FEV1/FVC ratio,Collect blood for serum chemistries including creatinine, electrolytes, total bilirubin, albumin, ALT, AST, total protein, CK, calculate CrCl, Ab tests,Collect mouth/nasal swabs for PCR tests,Collect urine for analysis, including pregnancy test (in women),Collect serum on-site as the back-up storage (3 mL serum) andCollect dietary history.

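### Shedding duration, a primary outcome, is dated by swabs scheduled from discharge, so recorded values depend on length of stay unless shedding is analysed as interval-censored

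*Protocol article*

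**What the plan says.** All of the following is in the protocol article.

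- **Outcome** (Primary outcome and secondary outcomes): shedding duration is a primary outcome, defined as "the time from the first positive RT-PCR results to the occurrence of the last positive RT-PCR results or negative RT-PCR results".
- **In hospital** (Sample size and sampling procedures): "all patients will be followed-up daily until discharge according to WHO and National discharging guideline". No swab is named and the discharge criteria are not reproduced.
- **Sampling** (Data collection): biological samples are "collected at baseline and follow up when samples are taken in the context of care". Study population adds that "follow-up will be done strictly within the management adapted to their infection".
- **After discharge** (Sample size and sampling procedures): "Enrolled cases will be followed up at 2 weeks, 3 months, 6 months, 9 months, and 12 months post-discharge", and "A visit window of ± 7 days may be applied to these visits".
- **Swabs at those visits** (Follow-up visits): the task list includes "Collect mouth/nasal swabs for PCR tests", and the visit data are "used to ascertain primary and secondary outcomes".
- **Analysis** (Data processing and statistical analysis): Cox regression is named for time-to-event variables, with semi-parametric and parametric survival methods where appropriate. Interval censoring is not mentioned.

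**The concern.** The outcome clock starts at the first positive test, but the only dated swabs are counted from discharge. While a patient is in hospital, swabs may be days apart. After discharge the gaps are about 2 weeks and then about 2.5 months. Two patients who clear the virus on the same day can therefore be recorded with very different durations solely because one went home earlier. Asymptomatic cases followed at home have no clear discharge anchor at all.

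The study enrols every severity and wants to relate host factors and treatment to outcome. Those factors plausibly drive length of stay, and so swab spacing. If the swab date is used as the exact end of shedding, a regression can report an association that comes from the swab calendar. A larger sample does not remove it.

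Fixing the end event does not cure this. Dating by last positive cuts shedding short in patients discharged early, and dating by first negative stretches it.

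**Working it through.** The plan has no shedding figure to reproduce. Its sample size of 6,390 rests on a death rate and does not bear on this point. From the plan come the post-discharge visits, the ± 7 day window and the two possible end events. Shedding distributions, lengths of stay and in-hospital swab intervals are assumptions.

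**1. Single patients.** Swabs every 3 days in hospital and at discharge, then 14 and 91 days after discharge.

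- True shedding 20 days. With a 7-day stay, swabs fall on days 3, 6, 7, 21 and 98, so the last positive is day 7 and the first negative day 21. With a 21-day stay, the last positive is day 18 and the first negative day 21. The last-positive ratio is 18/7 = 2.6; the first-negative dates agree.
- True shedding 22 days. With a 7-day stay, the last positive is day 21 and the first negative day 98. With a 21-day stay, they are days 21 and 35. The first-negative ratio is 98/35 = 2.8; the last-positive dates agree.

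**2. Groups with variable stays.** Both groups have the same log-normal shedding (geometric SD 1.6). Stay is log-normal (geometric SD 1.3, medians 7 and 21 days) and independent of shedding. Swabs are daily in hospital and at discharge, then at the planned visits with the ± 7 day window. Recorded medians in days:

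| True median | Last positive, 7 v 21 | Fold | First negative, 7 v 21 | Fold |
|---|---|---|---|---|
| 10 | 6.6 v 10.0 | 1.5 | 19.6 v 11.0 | 1.8 |
| 14 | 7.6 v 13.0 | 1.7 | 23.2 v 15.0 | 1.5 |
| 20 | 10.8 v 17.6 | 1.6 | 28.6 v 23.5 | 1.2 |
| 28 | 17.5 v 22.3 | 1.3 | 95.3 v 36.2 | 2.6 |

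By last positive, the longer stay looks longer. By first negative, the shorter stay does. Daily in-hospital swabbing does not remove the difference.

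**3. Closer stays.** For median stays of 10 v 14 days and in-hospital swabs every 2, 3 or 7 days, the differences are mostly 1.0 to 1.3-fold. One setting (true median 28 days, first negative) reached 96.5/42.9 = 2.2-fold. There about half the longer-stay group is still positive at the 2-week visit, so the median jumps across the gap to 3 months and is unstable.

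**4. Cox regression on swab dates, stark contrast.** Shedding is log-normal with log-SD 0.5 in both groups. Group A is swabbed every 3 days to day 30, then on days 44 and 120. Group B is swabbed on days 3 and 6, discharged on day 7, then swabbed on days 21 and 97. The true hazard ratio and the true time ratio, B versus A, are both 1.0.

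| True median | HR, last positive | HR, first negative | Interval-censored time ratio |
|---|---|---|---|
| 10 | 2.05 | 0.38 | 1.006 |
| 14 | 2.14 | 0.47 | 0.999 |
| 18 | 2.29 | 0.56 | 1.000 |

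Repeat runs gave hazard ratios of about 2.0 to 2.4 and 0.38 to 0.58, and time ratios of 0.99 to 1.03.

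**5. Milder assumptions.** With variable stays and a discharge swab, the last-positive hazard ratio is 1.58 to 1.74 for medians of 7 v 21 or 7 v 14 days. For 10 v 14 days it is 1.25 to 1.35, and 0.97 to 1.15 by first negative. If discharge requires a negative swab (3-day grid, clinical stays 7 v 21 days), it is 0.99 to 1.03 on both end events.

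**The case against.** **The discharge rule.** This is the strongest objection. The stark scenario sends every group B patient home on day 7 whatever the PCR shows. At a true median of 14 days, Φ(ln 2 / 0.5) = 92% of them are still shedding. If the guideline in force requires a negative PCR, stay follows shedding and the distortion almost vanishes. The documents show neither rule, so this stands as a limit on the size. Cases followed at home would remain exposed.

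**The sampling sentence.** A reader might infer that PCR swabs are taken only when care happens to take them. The sentence covers biological samples in general, ties them to the research objectives and goes on to blood volumes. Consent also covers a nasopharyngeal swab. That reading is not supported. Nor does the lack of a swab in the baseline list matter, since entry already requires RT-PCR confirmation. What remains is that no in-hospital swab day is given and every dated swab hangs on discharge.

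**Left to the SAP or full protocol.** In-hospital swab days and censoring details may well be there, and their absence from an article is no fault. The article also does not rule out interval censoring. But it does define the outcome as a time ending at an observed swab and does name Cox for time-to-event variables. Followed as written, that produces the dependence on stay.

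**Conclusion.** The point holds as a cheap improvement to how a primary outcome is recorded and analysed. Taken as written, the outcome definition, the discharge-anchored swabs and Cox regression on swab dates make recorded shedding depend on length of stay.

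The size is illustrative. It runs from about 1.0-fold (similar stays, or discharge only after a negative PCR) to about 2 to 2.8-fold (stays of about 7 v 21 days or more, with discharge while still shedding). It rests on assumed shedding, stays and in-hospital swab intervals, and its direction depends on the end event.

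A reader might infer that a two-fold bias is established for this study. The documents do not support that, because they give neither lengths of stay nor discharge criteria.

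**What to change.** Record the date and result of every RT-PCR, including those done for care. Analyse shedding as interval-censored between the last positive and the next negative swab, instead of taking a swab date as its exact end. Carry patients discharged while positive into the post-discharge swabs.

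**Cost.** Two fields per swab, a standard interval-censored model, and wider intervals for patients discharged early. No test is added.

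**Limits.** The model cannot restore information lost between the 2-week and 3-month visits. It also assumes that swab timing, given the recorded results and covariates, carries no further information on shedding. The simulated time ratios came from fitting the same log-normal family that generated the data.

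**Not recommended.** Moving one post-discharge swab to a fixed day after the first positive test looks attractive but does not work by itself. In the stark scenario with exact dating, a day-14 swab gave last-positive hazard ratios of 1.8 to 5.0, and a day-21 swab left them at 2.2 to 2.3. Equal medians needed fixed swabs every 3 days to day 42 for everyone; weekly ones still left ratios of 0.90 to 1.35.

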**Methods:**

A multi-center cohort study design will be performed. Patients with confirmed COVID-19 infection admitted to selected treatment centers will be enrolled irrespective of their symptoms and followed-up for 12 months. Baseline epidemiological, clinical, laboratory and imaging data will be collected from treatment records, interviews, physical measurements, and biological samples. Follow-up data collection involves treatment and prognostic outcomes to be measured using different biomarkers and clinical parameters. Data collection will be done electronically using the Open Data Kit (ODK) software package and then exported to STATA/SPSS for analysis. Both descriptive and multivariable analyses will be performed to assess the independent determinants of the treatment outcome and prognosis to generate relevant information for informed prevention and case management. The primary outcomes of this study are death/survival and viral shedding. Secondary outcomes include epidemiological characteristics, clinical features, genetic frequency shifts (genotypic variations), and nutritional status.

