### Baseline assessment

The baseline assessment (day 1) will be scheduled immediately after screening. At baseline, the following tasks will be performed:Review and record all prior workup or test results.Record detailed history of prior medication use in the subject.The query for signs and symptoms and updated medications used since the screening visit. Any signs or symptoms reported after study drug administration should be recorded as adverse events. Any signs or symptoms reported before the study should be recorded as a pre-existing condition but should be collected and recorded in detail.Perform a complete physical examination.Obtain vital signs (HR, BP, RR, Oxygen saturation, capillary refill), Oxygen saturation (SpO2) with pulse oximetry.Obtain body height, weight, and waist circumference.Obtain the dietary history of the patients.Collect urine for urinalysis, with the microscopic exam and for a pregnancy test (in women).Collect blood for CBC and for serum chemistries including creatinine, total bilirubin, albumin, ALT, AST, total protein, CK, Creatinine Clearance (CrCl), and Ab assays, fasting blood sugar, lipid profiles (TC, LDL, HDL and triglycerides), plasm 25-hydroxy vitamin D concentration, laboratory test for D-dimers, platelet count, PT PPT, INR, and serum ferritin.Collect serum (recommend 5 mL serum storage at the investigational site as a back-up specimen).

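### Screening one to two days into the admission leaves earlier deaths out of the primary death outcome, so mortality is conditional on surviving to enrolment

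*Protocol article*

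**What the plan says.** Four statements in the protocol article fix the point at which a patient enters the cohort.

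- Data collection: "The screening will be performed within the period between one to two days of admission to the hospital".
- Baseline assessment: "The baseline assessment (day 1) will be scheduled immediately after screening".
- Sample size and sampling procedures: "After baseline assessment, all patients will be followed-up daily until discharge".
- Study population: the patient "consents to be enrolled in the follow-up study and provide all necessary information/data, blood sample, and nasopharyngeal swab for testing". A separate exclusion covers anyone "not capable of understanding or complying with the study protocol or provide consent".

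Death is a primary outcome. The abstract says "The primary outcomes of this study are death/survival and viral shedding". The section on primary and secondary outcomes lists "treatment outcome (active cases, recovered, death or transferred for further treatment), recovery time, and duration of viral shedding".

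The target is broad. Study population says patients are enrolled "irrespective of their differences (age, sex, symptoms, severity, and any other conditions". Aim and study setting refers to patients admitted to the treatment centres, and Study design and period describes the cohort as an unbiased collection of data. No section says how deaths between admission and screening are recorded.

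**The concern.** A patient who has died cannot consent or give blood and a swab. If screening starts one to two days after admission, deaths before that point fall outside the cohort. The observed death proportion is then conditional on surviving to enrolment, and it is too low as a description of admitted patients. The deaths lost are the fastest ones, which sits badly with the stated intention to enrol across all severities.

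Two features make this worth settling before recruitment. A larger sample does not reduce the error. Nor can a later analysis restore deaths that nobody logged, so an analysis plan could not repair the omission.

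**Working it through.** **The plan's own figure.** The only design figure is the sample size of 6,390, said to rest on a 28% death rate, a design effect of 2.5 and 20% loss to follow-up. No precision, power or effect size is given, so the figure can be neither confirmed nor refuted. If a single proportion with a two-sided 95% interval is assumed, the half-width can be back-solved:

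- Loss handled by dividing by 0.8: effective n = 6,390 × 0.8 / 2.5 = 2,044.8, and half-width = 1.96 × √(0.28 × 0.72 / 2,044.8) = 0.0195.
- Loss handled by multiplying by 1.2: effective n = 6,390 / (1.2 × 2.5) = 2,130, and half-width = 1.96 × √(0.28 × 0.72 / 2,130) = 0.0191.

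Either way it is about 1.9 points, but the plan does not state this value. Other designs also land within 3% of 6,390: a 99% interval with half-width 0.025 and loss multiplied by 1.2 gives 6,421, and a comparison of 28% with 22% at 90% power, also multiplied by 1.2, gives 6,558.

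**Sequence of entry.** Admission comes first, then screening at one to two days, then baseline at once, then daily follow-up. Consent and samples are needed to enter. A death before screening meets none of the entry conditions.

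**Size of the effect.** Let d be the true in-hospital death proportion among confirmed admissions and s the share of those deaths that occur before screening. Of N admissions, N(1 − ds) can be enrolled and Nd(1 − s) of them die, so

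observed = d(1 − s) / (1 − ds).

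The planning value d = 28% comes from the sample size section. The value d = 10% and all values of s are assumptions, because the documents give no s.

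| s | d = 28% | shortfall | d = 10% | shortfall |
|---|---|---|---|---|
| 5% | 0.266 / 0.986 = 27.0% | 1.0 points | 0.095 / 0.995 = 9.5% | 0.5 points |
| 10% | 0.252 / 0.972 = 25.9% | 2.1 points | 0.090 / 0.990 = 9.1% | 0.9 points |
| 20% | 0.224 / 0.944 = 23.7% | 4.3 points | 0.080 / 0.980 = 8.2% | 1.8 points |

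**Check that a log recovers the loss.** Take 1,000 confirmed admissions, 280 deaths and s = 10%. Then 28 die before screening, and the cohort shows 252 / 972 = 25.9%. Adding the logged deaths gives (252 + 28) / (972 + 28) = 28.0%.

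**The case against.** **The wording may allow earlier screening.** The sentence can be read as meaning during the first one to two days, and the assessment that follows is labelled day 1. This stands as an ambiguity. It is not the more natural reading of a window with a stated lower bound, and if day-of-admission screening is intended, one phrase would say so. A reader might infer that nobody can be enrolled on the day of arrival; the text does not go that far.

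**Any consented cohort loses patients who die before consent.** True. Earlier screening shortens the gap without closing it. Death after enrolment is also a valid outcome for those enrolled. The difficulty lies in presenting it as mortality among admitted patients. A screening log is often left to the full protocol, but this article itself fixes the entry time and makes the claims about the population.

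**The size is assumed.** Also true. The 28% is a planning value from a retrospective study, while this cohort enrols patients whatever their symptoms, and at 10% the shortfalls are small. Deaths during 12 months of follow-up would make the early share of all deaths smaller than its share of in-hospital deaths. A reader might infer that the bias exceeds the study's precision. That is not established, since the 1.9 points is back-solved from an assumed formula.

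**Two further inferences should not be drawn.**

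- A reader might conclude that the baseline markers (oxygen saturation, D-dimer, clotting tests, ferritin) are spoiled by treatment given before measurement. The protocol already collects earlier test results, prior and concomitant medication, therapeutic measures and oxygen support, so this can largely be handled in the analysis.
- A reader might conclude that factors which kill quickly must look weaker. Under proportional hazards, starting the clock at enrolment does not by itself weaken a Cox hazard ratio. Attenuation would need effects concentrated in the first hours, and the documents offer no evidence of that.

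**Conclusion.** The point holds for the death proportion. On the natural reading of the screening window, confirmed patients who die before screening are absent from the primary death outcome, and nothing in the document brings them back. The estimate is conditional on survival to enrolment, while the aim and the description of the cohort claim more.

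The direction is known: mortality among admitted patients is understated. The size is not. It runs from 1.0 to 4.3 points at a true 28%, and from about 0.5 to 1.8 points at a true 10%, for assumed early shares of 5% to 20%. If sites in practice screen from arrival, the effect shrinks to the short interval before consent.

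The correction is worth making before recruitment because it is cheap and the lost information cannot be rebuilt reliably afterwards. The conclusion does not extend to the usability of the baseline markers or to the estimated effects of risk factors.

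**What to change.** 1. In Data collection, reword the window so that screening runs from arrival up to day 2 of the admission.
2. Keep a count-level log at each centre, taken from its admission register, of RT-PCR-confirmed admissions and of deaths before enrolment.
3. Report mortality with the pre-enrolment deaths added, beside the cohort estimate, and state that the cohort estimate is conditional on survival to enrolment. Where not every surviving patient is enrolled, combine the two at the level of admissions: q + (1 − q) × cohort mortality, where q is pre-enrolment deaths divided by confirmed admissions. This assumes that survivors who are not enrolled die at the same rate as those who are. In the worked example, 0.028 + 0.972 × 0.2593 = 0.280.
4. Keep the protocol-timed day-1 marker values, and use the treatment and oxygen data already collected to account for care given before measurement. Do not replace them with the first routine values, whose availability may depend on severity and centre.

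The cost is a change of wording and modest register work at about 15 sites, with no extra visit or sample. The need for consent still leaves a short gap before entry, and the log makes the deaths in that gap visible.
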